#### **Data ownership**

Each investigator will be the owner of the data collected at the individual centers. The experimental data, shared for the realization of the current study, will be the equal property of the three principal investigators.

Each study derived from the data collected, will be shared between the 3 principal and co-investigators prior to being sent to scientific journals for publication.

#### **Expected results, possible problems and solutions**

The project aims to prove the reduction of more than 30% of unnecessary excisions, with <2% of melanomas with delayed diagnosis (compared with the delayed melanoma diagnosis associated with dermoscopy, which has an estimated range of 7.6- 16.2%. [*Salerni G et al JEADV 2012*), and no thin tumor (thickness > 0.5mm) diagnosed late. The integration of the RCM tool into the standard care pathway is estimated to demonstrate a possible saving of ~€ 30,000 /100,000 inhabitants / year. The risk of misdiagnosing a true melanoma with RCM is minimized, as patients with clinical/dermoscopically suspicious lesions are referred to digital dermoscopy follow-up, where any changes should be recognized within a short interval of time, without risk to the patient's health. The risk of patient loss to follow-up will be minimized, by the allocation of a follow-up appointment during the initial consultancy visit, with the activation of a dedicated telephone number for enrolled patients who may need to modify their pre-programmed follow-up. Additionally, patients who do not present for the pre-programmed consultancy visit will be contacted by telephone.

The cost-utility model, adaptable to different local situations, will be published and made available for the implementation of similar triage systems according to a radial model for the management of skin neoplasms.

The integration of RCM in the triage of high-risk patients will demonstrate the real advantages, by calculating RCM diagnosed melanomas which may have been misdiagnosed with video microscopy alone, due to the lack of significant dermoscopic features.

The risk of increasing the number of unnecessary excisions will be considered and verified periodically through an interim analysis every 6 months.

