**Exclusion criteria:**

- 1) Patients <18 years old
- 2) Comorbid dermatological pathologies that can alter the visualization of the lesions in RCM, such as extensive hyperkeratotic skin diseases or widespread eczema.
- 3) Physiological, general pathological or psychiatric conditions that prevent the patient from being able to lie down for at least 10 minutes (time of RCM evaluation)
- 4) lesions with alterations (ulceration, crust, hyperkeratosis) which prevent RCM visualization.

Additionally, in a smaller population of patients classified at high risk of melanoma, will be evaluated with a total body examination with the RCM (VivaScope 3000) for each melanocytic skin lesion in addition to classic videomicroscopy. Suspected lesions in dermoscopy and / or RCM will be excised. Subsequently, the accuracy of excisions will be compared for both groups, and the benefit of the combined approach to the patient will be calculated. A population of about 300 patients at high risk of developing melanoma (> 100 nevi, > 4 atypical nevi) will be required. These tests will be performed in two of the collaborating outpatient clinics, performed by 2 interchangeable expert specialists (both will examine 50% of the population with dermoscopy and 50% with RCM). Coincident and

discordant data in case of equivocal injury will be compared. Any lesion showing features in dermoscopy and / or confocal that are suspicious of melanoma will be excised. In high-risk patients, any lesions that do not show clear benign features will be routinely monitored with digital videodermoscopy for at least six-months.

The main objective in this case is the quantification of detection of suspected and confirmed malignant lesions on histological examination after excision, with respect to the standard of care (clinical examination + videomicroscopy). The time required for the total-body examination will be measured and compared with a standard videomicroscopy to estimate the cost-benefit value of the procedure.

The previously described statistical tests (chi-square and Z-test) will be applied.

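### High-risk sub-study: RCM's advantage is to be shown by a count of RCM-only melanomas, which can never be negative and so is not by itself evidence of advantage

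*Protocol*

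**What the plan says.** The high-risk sub-study is described in the Protocol in the text that follows the list of exclusion criteria.

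- **Size:** "A population of about 300 patients at high risk of developing melanoma (> 100 nevi, > 4 atypical nevi) will be required". No effect size, power or significance level is given for this part.
- **Design:** the manual RCM instrument is used "for each melanocytic skin lesion in addition to classic videomicroscopy". Each lesion is therefore read by both methods and the data are paired.
- **Excision:** "Suspected lesions in dermoscopy and / or RCM will be excised", and again "Any lesion showing features in dermoscopy and / or confocal that are suspicious of melanoma will be excised".
- **Comparison:** "Subsequently, the accuracy of excisions will be compared for both groups, and the benefit of the combined approach to the patient will be calculated". Concordant and "discordant data in case of equivocal injury will be compared". The main aim is to quantify suspected and confirmed malignancies against standard care, using the chi-square and Z tests named for the main trial.

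The principal objectives under Scope of the Project add sensitivity and specificity of the manual tool in high-risk patients.

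The section Expected results, possible problems and solutions then states how the benefit will be shown: RCM in this group "will demonstrate the real advantages, by calculating RCM diagnosed melanomas which may have been misdiagnosed with video microscopy alone". Its next sentence says that a possible rise in unnecessary excisions will be checked at six-monthly interim looks. It does not connect that check to the claimed advantage.

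**The concern.** The sentence in Expected results makes one number the means of demonstration: melanomas that RCM identified and videomicroscopy did not. It names neither of the quantities that could count against RCM, namely melanomas seen by videomicroscopy and missed by RCM, and benign lesions removed only because RCM flagged them.

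Under the either-positive excision rule, such a count cannot come out unfavourably. A second dermoscopic reading could produce a positive count too, and even flagging lesions at random would on average pick up some melanomas. The count alone cannot separate a useful add-on from an uninformative one.

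At stake is the conclusion on one of the three principal objectives, and the argument in Meaning and innovation that closer examination of high-risk patients is worthwhile.

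**Working it through.** **Step 1. What the count can show.** Classify each histologically confirmed melanoma by the two readings:

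| | Videomicroscopy + | Videomicroscopy − |
|---|---|---|
| RCM + | a | b |
| RCM − | c | not excised on either reading |

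- Videomicroscopy alone finds a + c.
- The combined approach finds a + b + c.
- Combined minus videomicroscopy = b, which is never below 0.
- RCM minus videomicroscopy = (a + b) − (a + c) = b − c, which can be negative.

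The Expected results sentence uses b only. Because either positive reading leads to excision, b and c are both observable, and so are the benign lesions excised on RCM alone.

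**Step 2. Inputs.** The figure of about 300 patients has no stated inputs, so it cannot be reproduced, and it does not enter this check. The Protocol gives no expected number of melanomas M, no sensitivities and no correlation between the methods' errors in this sub-study. All values below are assumptions.

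**Step 3. How often b is at least 1.** With p the chance that a melanoma is RCM-only, P(b ≥ 1) = 1 − (1 − p)^M. For independent errors, p = (RCM sensitivity) × (1 − videomicroscopy sensitivity).

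| Assumption | p | M = 3 | M = 6 | M = 10 | M = 20 |
|---|---|---|---|---|---|
| Equal, both 0.85, independent | 0.85 × 0.15 = 0.1275 | 34% | 56% | 74% | 93% |
| Equal, both 0.95, independent | 0.95 × 0.05 = 0.0475 | 14% | 25% | 39% | 62% |
| Equal, strongly correlated errors | 0.02 (set directly) | 6% | 11% | 18% | 33% |
| RCM worse: 0.75 against 0.85, independent | 0.75 × 0.15 = 0.1125 | 30% | 51% | 70% | 91% |
| RCM worse: 0.70 against 0.90, independent | 0.70 × 0.10 = 0.07 | 20% | 35% | 52% | 77% |

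For equal sensitivities s and error correlation ρ, p = s(1 − s)(1 − ρ). So p = 0.02 means ρ = 1 − 0.02/0.0475 = 0.58 at s = 0.95, or ρ = 1 − 0.02/0.1275 = 0.84 at s = 0.85.

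With equal methods the chance thus runs from about 6% (M = 3, strong correlation) to over 90% (M = 20, both 0.85, independent). It passes one half only with roughly 6 to 10 or more melanomas, moderate sensitivities and near-independent errors. The ends of the range move with the assumptions.

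**Step 4. Using both discordant cells.** An exact McNemar test at two-sided 0.05 was applied to b and c, with M from 3 to 30, independent errors, and RCM equal or worse. The chance of a significant result favouring RCM was at most 0.9% (both 0.85, M = 30). At both 0.85 it was 0.03% for M = 10 and 0.5% for M = 20.

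The test is demanding at such counts. Five discordant melanomas all in RCM's favour give 2 × 0.5^5 = 0.0625, and six give 2 × 0.5^6 = 0.031. At least six RCM-only melanomas with no videomicroscopy-only ones are needed before it can reach 0.05.

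**The case against.** **The Protocol does not rely on this count alone.** A reader might infer that the sub-study counts only melanomas favouring RCM. The documents do not support that. The sub-study text plans to compare the accuracy of excisions and the discordant data without restricting direction, and the principal objectives include sensitivity and specificity. All of these can go against RCM. This stands, and it limits the point to the stated basis of the claimed advantage.

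**There is no decision rule.** The sentence is forward-looking narrative with no threshold or test. Treating one RCM-only melanoma as success is a reading made here to gauge size. This stands too. A formal criterion could sit in an analysis plan that is not at hand, and its absence is not the point. The sentence nevertheless says by what means the advantage will be shown, and that means is a poor one.

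**RCM is an add-on.** It is used besides videomicroscopy, so melanomas that RCM misses and videomicroscopy catches are still excised and are no loss to the combined pathway. Extra melanomas are a legitimate measure of benefit. This is correct, and it means that b − c must not decide the add-on claim, since that difference addresses RCM as a replacement. But extra melanomas support an add-on only when weighed against the extra benign excisions. The Protocol leaves those to periodic interim checks and to a general comparison of excision accuracy, without linking either to the claim.

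**The consequence for the cost model is not shown.** The sub-study text ties its cost-benefit estimate to measured examination time, and nothing shows the RCM-only count entering the economic model. No such consequence is claimed here.

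**Conclusion.** The point holds in a limited form. The Expected results section rests the claimed advantage in high-risk patients on a count that the either-positive excision rule keeps at zero or above whatever RCM's accuracy. The comparisons planned elsewhere in the Protocol could show a disadvantage, but this section does not base its claim on them.

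That the one-directional count cannot be negative follows from the text and needs no assumption. How often it would suggest an advantage does rest on assumptions. With equally sensitive methods, the chance of at least one RCM-only melanoma is about 6% to over 90% across the values tried. A reader might go further and say that an advantage would usually be reported even if RCM were no better or worse. That cannot be sustained, because it fails with few melanomas, high sensitivities or correlated errors, and the Protocol fixes none of these.

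**What to change.** Reword the sentence in Expected results so that it agrees with the principal objectives and the sub-study text:

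1. Base the add-on claim on incremental yield: RCM-only melanomas together with RCM-only benign excisions, expressed as benign excisions per extra melanoma with a 95% confidence interval.
2. Report videomicroscopy-only melanomas beside the RCM-only ones, with the paired difference and its exact 95% confidence interval. Use that difference only for a statement that RCM detects more melanomas than videomicroscopy, not to judge the add-on.
3. State that a non-zero RCM-only count is not, on its own, evidence of advantage.

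The excision rule stays as it is. The cost is a change of wording and a small extra table. Lesions suspicious on either method are already to be excised and examined histologically, so no further patients, readers or procedures are needed. The drawback is that with few melanomas the interval will be wide. The conclusion may then be inconclusive and less favourable to RCM than the present wording anticipates.

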#### **Meaning and innovation**

If RCM is proven to be an effective tool in avoiding unnecessary excisions, the integration of RCM within a radial model (such as that developed in this study) may be appropriate for the National Health System. The benefits of a more accurate examination of patients at high-risk of melanoma could save the high costs of treating advanced cancers.

The overall impact of this study will be to influence health management for skin cancer patients, by creating a more efficient and less expensive diagnostic triage model. For the Principal Collaborating Center, the research group will be composed of trained personnel (with years of RCM experience and internationally recognized RCM expertise, along with numerous scientific publications in the field of non-invasive oncological diagnostics with dermoscopy and RCM). The Principal Collaborating Center will also coordinate the prospective study on diagnostic efficacy and the cost-benefit estimate for the implementation of RCM in the triage of skin cancers. The collaboration with the Department of Pharmacological Sciences of the University of Pavia will ensure the development of an adequate and dedicated cost-benefit model. The sub-study assessment (with manual RCM) in the early diagnosis of superficial melanomas, will also include a team with a high level of

expertise for both dermoscopy and RCM. The other Collaborating Centers, in addition to participating in the prospective randomized study, will focus on the application of manual RCM in other complex clinical situations, such as the early diagnosis of lentigo maligna and pre-surgical definition of initial basal cell carcinoma. Overall, a complete picture of the advantages and limitations deriving from the use of the manual RCM for cutaneous neoplasm diagnosis will be calculated and an estimate of its cost-utility will be performed. Resources available for the project

- 3GDermLite manual dermatoscope (2 devices). DermLite is a patented technology dermatoscope that combines non-polarized light dermoscopy for use with refractive liquid and polarized light dermoscopy for use with or without skin contact.

This versatile device offers the ability to screen many lesions in the same patient within seconds.

- Vidix digital videodermatoscope (two devices): this is a digital videodermatoscope that allows the visualization and storage of clinical and dermoscopic images. The camera has all the controls: display, photograph images, select magnifications, modify the acquisition parameters, modify the brightness, allow the passage from dermoscopy mode to the clinic and vice versa. This digital dermatoscope has several advantages: a digital camera with autofocus and automatic zoom and the ability to acquire images with different magnifications from 7x to 100x (clinical image, polarized image and magnifications), has a new, more intuitive software for faster and more accurate management of patient images and archives.

- VivaScope 1500® RCM (1 device): The VivaScope 1500 is an industry-leading in vivo RCM device for the observation and capture of in vivo images. The instrument is paired with a VivaCam® dermoscopic digital camera. When recording with VivaScope 1500, the captured dermoscopic images can be used to precisely navigate the area of interest. The camera integrated within the VivaScope 1500 allows you to capture and record clinical photographs of an area of interest, onto which a map of the areas analyzed can be nominated.

### **Conclusion**

This study aims to define an ideal triage for skin cancer patients within a Regional radial system, with reference centers equipped with RCM, able to perform virtual biopsies in high-risk patients before and/or instead of surgical excision.

The increased diagnostic accuracy should be useful in reducing waiting lists and offering cost savings related to reduced surgery / histopathology procedures. The data will produce guidelines based on the evidence-based medicine model, the cost-benefit model and the risk analysis for the integration of RCM in the clinical diagnosis phase of skin cancer.
